***Moderation of Effectiveness Outcomes by Implementation Factors***

Moderation analysis using OLS regression will be used to determine whether program impacts vary based on CFIR contexts. Regression models will be built on those in Aim 2. Multiplicative interaction terms between group assignment and individual moderators will be added.

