# Protocol Summary

| Title | HEALTHYSTEPS + PLAYREADVIP EFFECTS ON PARENTING AND CHILD DEVELOPMENT: A RANDOMIZED IMPLEMENTATION EFFECTIVENESS TRIAL |
| --- | --- |
| Short Title | HealthySteps + PlayReadVIP |
| Brief Summary | This study aims to investigate the effectiveness and implementation outcomes for the integration of two evidence-based practices and interventions (EBPIs) within pediatric primary care settings: HealthySteps (HS), which provides parenting support, and PlayReadVIP, which promotes relational health through video coaching. Families will be randomized to receive either the integrated HS + PlayReadVIP model or traditional HS, and we will examine impacts on parenting, parent-child relationships, and child development, as well as feasibility, acceptability, and appropriateness of the integrated intervention. |
| Phase | Phase 3 |
| Objectives | This study aims to:  1) Assess the effectiveness and implementation of combining the HealthySteps (HS) parenting support model with PlayReadVIP to improve parenting and relational health outcomes.  2) Evaluate mechanisms of intervention impact, including mediation through social determinants of health and moderation by implementation outcomes. |
| Methodology | Randomized hybrid effectiveness-implementation trial |
| Endpoints | Parenting practices, parent-child relationships and child development, as well as feasibility, acceptability, appropriateness, and reach. |
| Study Duration | 5 years |
| Participant Duration | 2 years |
| Duration of behavioral intervention | 2 years |
| Population | 500 parent/infant dyads + 25 care providers |
| Study Sites | NYU Langone Health - Sunset Park Family Health Centers |
| Number of participants | 1025 participants |
| Description of Study Intervention/Procedure | The intervention being evaluated in this study integrates two evidence-based programs, HealthySteps (HS) and PlayReadVIP, into a combined model HS+PlayReadVIP to promote early childhood development and parent-child relational health. The integrated intervention will be implemented during routine pediatric well-child visits for families identified as Tier 3 (increased risk and reduced resources) by the HealthySteps Specialist. |
| Reference Therapy | Standard HealthySteps program |

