## Primary Objective

There are two primary objectives of this study:

**Aim 1. Implement the optimized integrated HS+VIP model (formalized in Aim 1), and conduct an effectiveness-implementation study (Hybrid I design).**

1. Examine effectiveness of the integrated HS+VIP model, including parent mental health, parenting behavior, and early child development outcomes.
2. Examine implementation outcomes, including reach, appropriateness, acceptability, feasibility, and fidelity, using an integrated RE-AIM^18^ and CFIR^19^ framework.

**Aim 2. Examine health disparities mechanisms underlying effectiveness-implementation outcomes.** Using a mixed methods design, we will examine whether HS+VIP impacts are 1) mediated by impacts on parent assets/vulnerabilities and ERH or 2) moderated by CFIR contextual factors or RE-AIM domains.

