## Total Number of Participants and Sites

Recruitment will end when 500 parent-child dyads and 25 care providers are enrolled. Recruitment and enrollment will take place at NYU Langone Sunset Park Family Health Center (SPFHC).

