**Assessment Procedures**

Assessments will be conducted at 12M and 24M (critical transition points for both parenting and child development) by highly trained, bilingual research staff, masked to intervention condition, to reduce bias. Assessments will last ~1 hour, in line with prior studies of parents of young children. Assessments will include surveys/questionnaires, observations of parents and children, and direct child assessments.

Outcomes to be assessed via questionnaire include:

|  | | | | | |
| --- | --- | --- | --- | --- | --- |
| **Level** | **Construct** | **Instrument** | **Base-line** | **12M** | **24M** |
| Effectiveness Outcomes | | | | | |
| Parent | **Parent-Child Relationship Quality** | Adult-Child Relationship Scale (*α*=.69-.84)^142^ |  | x | x |
|  | **Responsivity/Cognitive Stimulation** | StimQ Reading, Teaching/Play, Verbal Responsivity (*α*=.88)^143^ |  | x | x |
|  | Stress/Mental Health | Edinburgh Depression Scale (*α*=.77-.86)^144^, Perceived Stress Scale ( *α*=.75-.91);^145^ | x | x | x |
|  | Self-Efficacy | Parenting Self-Agency Measure (*α*=.68-.7)^146^ | x | x | x |
|  | Social Support | General Life Satisfaction (*α*=.91),^147^ Dyadic Adjustment Scale (*α*=.7-.95)^148^ | x | x | x |
|  | Structure | limit-setting, proactive parenting, feeding/sleep/screentime routines,^149^ Socolar Discipline Survey (*α*=.56-.82)^150^ |  | x | x |
|  |  | HealthySteps Parent Feedback Survey^170^ |  | x | x |
|  |  | Parenting Daily Hassles^171^ |  | x | x |
| Child | **Social Competence** | Infant Behavior Questionnaire (*α*=.75-.78),^151^ Brief Infant Toddler Social-Emotional Assessment (*α*=.69-.8)^152^ |  | x |  |
|  |  | Child Behavior Checklist (α=.9-.94)^153^ |  |  | x |
|  | Language & Cognitive Development | Early Social Communication Scale (*α*=.61-.91),^154^  MacArthur-Bates Communicative Development Inventories (*α*=.86);^155^  Dual Language Learners English-Spanish Inventories^172^ |  | x | x |
| Implementation Outcomes (CFIR, RE-AIM, CIHS) | | | | | |
| EBPI Provider (care-team member) | Acceptability | Acceptability of Intervention Measure (AIM; *α*=.89)^158^ |  | x | x |
|  | Appropriateness | Intervention Appropriateness Measure (IAM; *α*=.87)^158^ |  | x | x |
|  | CFIR Domains | Evidence-based Practice Attitudes Scale-36 (*α*=.80),^159^ clinic culture, perceived complexity of intervention, external policies, competence | x | x | x |
|  | Acceptability | Parent satisfaction surveys^117^ |  | x | x |
|  | | | | | |

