In addition, we will assess parent-child relationship quality through observation of videotaped interactions between parents and children at 12 months and 2 years, including play, shared reading, and teaching activities, with global coding of parent and child interaction quality (e.g., responsiveness, sensitivity, positive/negative regard).^138-141^

Direct assessment of child language development using the Receptive and Expressive One-Word Picture Vocabulary Tests^156,157^ will be conducted at the 2 year assessment.

Finally, qualitative interviews will be conducted to examine implementation outcomes, including:

| **Level** | **Domains** | **Measure** | **Base-line** | **12M** | **24M** |
| --- | --- | --- | --- | --- | --- |
| EBPI Provider (care-team member) | Acceptability | ease of program delivery, confidence/efficacy of program delivery |  |  | x |
|  | Appropriateness | perception that program meets needs of patient population |  |  | x |
|  | Fidelity | adherence and perceptions of program delivery |  |  | x |
|  | CFIR Domains | clinic culture, perceived complexity of intervention, external policies, competence |  |  | x |
|  | Acceptability | Parent satisfaction with intervention components |  |  | x |
| Parent | Appropriateness | perceptions that needs are met, content/coverage/frequency/ duration of program sessions, “essential” components |  |  | x |
|  | CFIR Domains | home environment, family needs, resources, motivation |  |  | x |
|  | CFIR Domains | home environment, family needs, resources, motivation |  |  | x |

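### Aim 2 moderation admits moderators that cannot be crossed with arm in a one-clinic trial or that arise after randomisation; it should be confined to baseline family-level variables

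*Protocol*

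**What the plan says.** **The analysis.** Protocol Section 9.1 (Moderation of Effectiveness Outcomes by Implementation Factors): "Moderation analysis using OLS regression will be used to determine whether program impacts vary based on CFIR contexts". The form is fixed in the same paragraph: "Multiplicative interaction terms between group assignment and individual moderators will be added".

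**The aim.** Section 3.1, Aim 2, asks whether programme impacts are "moderated by CFIR contextual factors or RE-AIM domains". The Protocol Summary lists "moderation by implementation outcomes" among the objectives.

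**The setting.** Section 5.6 names one health centre and adds: "Recruitment will end when 500 parent-child dyads and 25 care providers are enrolled". Section 4.1 gives that clinic 10 pediatric providers.

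**The measures labelled CFIR (Section 7.1.1).** In the questionnaire table they are provider surveys: an attitudes scale plus "clinic culture, perceived complexity of intervention, external policies, competence", at baseline, 12M and 24M. In the interview table the parent domains are "home environment, family needs, resources, motivation", marked at 24M only.

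**The RE-AIM measures (Section 9.1, Implementation Outcomes).** Reach compares the sample with the clinic population, and enrolled with declining families. Fidelity is summarised over sessions, separately for VIP and HS content. Engagement is the proportion of visits attended. Engagement and acceptability are both to be compared between arms.

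**Baseline family data.** Section 7.3.2 collects the home environment, social determinants and parent mental health at enrolment. The questionnaire table marks stress and mental health, self-efficacy and social support at baseline. Sections 7.1.1 and 9.6.1 place baseline before randomisation.

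**Power.** Section 9.5 claims more than 80% power with 400 families at alpha .05 for f² = .04 in the most complex regression, moderation included.

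**The concern.** An arm-by-moderator product term answers whether the programme works better for some families only if the moderator varies between families, is defined in both arms, and is not itself changed by arm. Several of the moderators that the aim and the analysis section name fail one of these conditions.

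If the plan is followed literally, some interactions cannot be fitted. Others can be fitted but may report, as contexts in which the programme works, differences in which families attended, engaged or were satisfied under each arm. Moderation is one of the two questions in Aim 2, so this bears on a stated objective.

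**Working it through.** **1. The plan's power figure.** Inputs from Section 9.5: N = 400, alpha .05, f² = .04. Assumed: two-sided test, 15 model terms, outcome SD 1, 1:1 allocation. Power comes from the noncentral F with λ = f² × N = .04 × 400 = 16.

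| Interaction terms tested jointly | Power |
|---|---|
| 1 | 97.9% |
| 5 | 88.5% |
| 8 | 82.0% |
| 10 | 78.1% |

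So the claim reproduces for family-level moderators with up to about eight terms. The main comparison (d = .30, 200 per arm) also reproduces, at 85%.

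**2. What f² = .04 means.** For a moderator that splits families into two equal halves, f² = δ²/16, where δ is the difference in arm effect between the halves. Then δ = √(16 × .04) = 0.80 SD, which is 0.80/0.30 = 2.7 times the assumed main effect. For a standardised continuous moderator f² = g²/4, so g = 0.40 per SD.

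| δ (SD) | f² = δ²/16 | Power, N = 400, one term |
|---|---|---|
| 0.15 | .0014 | 12% |
| 0.30 | .0056 | 32% |
| 0.45 | .0127 | 61% |
| 0.60 | .0225 | 85% |
| 0.80 | .0400 | 98% |

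The smallest difference detectable with 80% power is f² = .020, or δ = 0.56 SD. For δ = 0.30 about 1,400 analysed families would be needed.

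**3. Moderators that cannot be crossed with arm.** The design columns are 1, A, W, A×W.
- One clinic-level value, W = c: the columns become 1, A, c, cA. Rank is 2 of 4. Reach has no family-level score either, so the same applies.
- VIP-content fidelity, coded zero in controls: A×W equals W. Rank is 3 of 4. If it is left missing, every control family drops out and arm is constant.

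**4. Moderators that arise after randomisation.** Illustration with no true moderation, arm coded ±½ and an unmeasured family trait U:
- outcome Y = 0.3A + 0.5U + error, with error variance .75;
- moderator M = 0.5A + (0.5 + 0.5A)U + error, with error variance 1.

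The slope of M on U is b = .75 in one arm and .25 in the other. The slope of Y on M within an arm is 0.5b/(b² + 1), giving .375/1.5625 = .240 and .125/1.0625 = .118. The difference, .12, is a spurious interaction. In 2,000 simulated trials of 400 families the mean interaction was 0.12 and 29% of tests rejected. A baseline moderator gave about 0 and 6%. The parameters are assumed, so this shows the mechanism and does not predict the size of the bias.

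**5. Provider-level moderators.** Suppose families of both arms were linked equally to J providers, with the arm effect varying between providers with SD τ (assumed range below). The variance of the provider-specific arm effect is τ² + 4/(400/J). Plain OLS uses only the second part.
- J = 25: 4/16 = .25. For τ = 0.2 to 0.4 the standard error is too small by a factor of √(.29/.25) = 1.08 to √(.41/.25) = 1.28, so type I error is 7% to 13%.
- J = 10: 4/40 = .10. The factor is √(.14/.10) = 1.18 to √(.26/.10) = 1.61, so type I error is 10% to 22%.

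With clustering allowed for, power at g = 0.40 over τ = 0 to 0.4 is 97% to 85% for J = 25, 94% to 59% for J = 10, and 76% to 28% for J = 5.

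**The case against.** Four points can be made for the plan.

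**Sound moderators exist.** Section 9.1 (Moderation of Implementation Outcomes) treats family and child characteristics as CFIR factors, and Section 7.3.2 collects the home environment and social determinants before randomisation. This stands. It would be wrong to infer that the whole moderation analysis fails.

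**The analysis paragraph names only CFIR contexts.** No model in Section 9.1 writes out an arm-by-fidelity term, and an exact moderator list is commonly left to the SAP. This stands in part. The missing list is not the point. Aim 2 and the Protocol Summary expressly commit to RE-AIM domains and implementation outcomes, and the paragraph's own heading refers to implementation factors.

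**Provider views of the clinic can differ.** Clinic culture and external policy are surveyed person by person, and providers also answer before implementation (Care Provider Study Procedures). So only a single clinic summary is constant. The individual scores meet a different obstacle: the Protocol describes no link from families to providers, and plain OLS ignores clustering by provider.

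**Clinic and provider factors are already studied qualitatively.** That is so, and it makes the remedy easier.

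A reader might also infer that 25 providers put the moderation tests far below the stated power. Taking n = 25, the detectable correlation is tanh(2.802/√22) = .53, so f² = .286/.714 = .40, ten times .04. The documents do not support that reading. It describes a regression across providers alone, whereas the plan has a family-level regression with arm randomised family by family. If families of both arms are linked to 25 providers, power at the stated effect stays at 85% or more over the range tried.

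**Conclusion.** The concern holds for three classes of moderator that the Protocol admits:
- **Not estimable:** any single clinic-level value, reach as defined, and VIP-content fidelity.
- **Open to bias:** engagement, acceptability, other fidelity scores and the 24M parent interviews, because arm may change them and their interactions would mix selection with moderation.
- **Not ready for plain OLS:** provider-survey scores, for want of a family-to-provider link and of any allowance for clustering.

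It does not hold for baseline family-level variables, which are sound and already collected.

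The power statement in Section 9.5 is arithmetically right for family-level moderators but corresponds to a very large interaction. A difference in arm effect of 0.80 SD between halves is well covered; one as large as the whole assumed main effect, 0.30 SD, has about 32% power.

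These figures assume a two-sided test, 15 model terms, unit outcome SD, equal arms and, for providers, equal numbers of families each and τ from 0 to 0.4. The two rank results need none of these assumptions.

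**What to change.** 1. In Aim 2 (Section 3.1), the Protocol Summary and Section 9.1, limit tests of effect moderation to family-level variables measured before randomisation: home environment, social determinants, parent mental health, self-efficacy and social support.
2. Report clinic-level CFIR factors and reach descriptively or qualitatively.
3. Report engagement and fidelity as a dose-response within the HS+PlayReadVIP arm, labelled non-causal. A complier-average effect is optional; it answers a different question from moderation.
4. If provider-level scores are used, record which provider serves each family and account for clustering.
5. In Section 9.5, state that f² = .04 applies to family-level moderators, that it equals about 0.80 SD between two equal halves, and that power for a 0.30 SD difference is about 32% at N = 400.

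The main change is rewording with a little extra analysis, and it needs no new family data. Provider linkage would have to be recorded only if item 4 is taken up. The trial gives up a quantitative claim about clinic context, which one site cannot support.

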***Moderation of Implementation Outcomes***

To examine how CFIR individual and intervention-related factors predict implementation fidelity, multivariate regression analysis will be used. We will regress fidelity outcomes (fidelity in delivery, receipt, and enactment) on parents’ perception about the intervention, family characteristics, and child characteristics. Three fidelity outcomes will be examined in separate analyses.

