### Intermediate Visits

**Visit 2 (Day 180 +/- 90)**

- Record adverse events as reported by participant or observed by investigator.
- Administer questionnaires/surveys of parent well-being, parenting, and child development, and conduct parent-child observations
- Administer questionnaires to parents and care providers regarding program acceptability, appropriateness, and reach.
- Record participant’s engagement to intervention program and program fidelity and reach.

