***Implementation Outcomes***

Initial analyses will include examination of measure distribution, tests of normality, and confirmatory factor analysis, to create multi-indicator, multi-informant constructs where appropriate. Reach: Effect sizes of differences between 1) the study sample and clinic population, and 2) those who were eligible and enrolled vs. those who were eligible and declined will be determined by descriptive comparisons of multiple sociodemographic characteristics, including race/ethnicity, maternal age, child gender, and income. Fidelity: Summary scores will be created for fidelity data across sessions (i.e., computing proportion of HS and/or VIP session components completed on average, and the interquartile range). Scores will be computed separately for VIP (PCEs related) and HS (ACEs related) content for component analysis to understand whether differential implementation outcomes/challenges occur when HS+VIP is implemented jointly. Engagement: Chi-square tests for independence will be used to examine differences between the proportion of visits attended in the HS+VIP and standard HS models.

Acceptability: To investigate acceptability among parent participants, SEM will be used to examine AIM scores across assessment timepoints and to examine whether trajectories in parent AIM scores vary by participation or sociodemographic characteristics. In addition, multivariate ANOVA will be used to examine acceptability across interested parties at different levels (parents, HS+VIP care team). Finally, confirmatory factor analysis will be used to create a multi-informant acceptability construct and multivariate ANOVA will again be used to examine differences in overall acceptability across HS+VIP and standard HS groups.

Appropriateness: Analysis of appropriateness will mirror analyses used to examine acceptability.

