### Adherence and Retention Analyses

Participant engagemet in the intervention (e.g., number of possible sessions attended) and fidelity of intervention delivery (e.g., number of program components delivered at each session) will be tracked from the medical record and presented using summary statistics. As noted above, missing data and attrition analyses will be conducted to determine if data is missing at random or missing completely at random, and multiple imputation will be used to account for missing data.

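### Parents' perception of the programme is entered as a predictor of fidelity, although it is first measured at 12M, after part of the sessions being scored have been held

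*Protocol*

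**What the plan says.** The purpose is stated in section 9.1, Moderation of Implementation Outcomes: "To examine how CFIR individual and intervention-related factors predict implementation fidelity, multivariate regression analysis will be used". The model follows: "We will regress fidelity outcomes (fidelity in delivery, receipt, and enactment) on parents’ perception about the intervention, family characteristics, and child characteristics". The three outcomes, "fidelity outcomes (fidelity in delivery, receipt, and enactment"), are to be analysed separately. The paragraph does not say which wave of perception is used, nor which sessions make up the outcome.

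The fidelity score is described in section 9.1, Implementation Outcomes, as a summary across sessions: "computing proportion of HS and/or VIP session components completed on average". Section 9.4.2 adds that "fidelity of intervention delivery (e.g., number of program components delivered at each session) will be tracked from the medical record".

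Parents' views of the programme come from three places:

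- The measures table in section 7.1.1 lists "Parent satisfaction surveys" with the baseline column empty and marks at 12M and 24M. The HealthySteps parent feedback survey has the same pattern.
- Visit 2 (section 7.3.3) and the final visit (section 7.3.4) each include the instruction "Administer questionnaires to parents and care providers regarding program acceptability, appropriateness, and reach".
- Parent interviews, at 24M only, cover "perceptions that needs are met, content/coverage/frequency/ duration of program sessions".

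Delivery starts at infant age 4 months according to section 6.1.1, which gives nine sessions running to 36 months. The randomization paragraph of section 7.1.1 instead has families receiving the programme at each well-child visit through 24M.

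**The concern.** A predictor should be fixed before the outcome it is said to predict. Here the parent forms an opinion during delivery, the survey records it, and the opinion is then used to explain a score that includes the sessions that shaped it. A positive coefficient could mean that receptive parents get fuller delivery, or simply that fuller delivery leaves parents more satisfied. The planned regression cannot separate the two, yet its stated purpose invites the first reading.

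At stake is one of the Aim 2 analyses of how implementation works. A team planning roll-out might try to raise fidelity by changing parents' attitudes when the association runs the other way. The intention-to-treat comparison of the two arms is not touched.

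**Working it through.** The plan gives no figure on this point to reproduce. The check sets the measurement schedule against the session schedule.

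**Time order**

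1. First session: 4 months (section 6.1.1).
2. First measurement of parents' perception: the 12M assessment (sections 7.1.1 and 7.3.3).
3. Fidelity score: an average over sessions (section 9.1), with no restriction to sessions after the survey.
4. So every session held before the 12M survey enters the outcome but precedes the predictor.

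**How many sessions**

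The protocol does not list session ages, so the grids below are assumptions. Section 6.1.1 gives 9 sessions over 4 to 36 months. Section 9.5 gives 7 to 10 sessions per family over 2 years. Evenly spaced session i of n between ages a and b falls at a + (b − a)(i − 1)/(n − 1). For example, 9 sessions over 4 to 36 months have a step of 32/8 = 4 months, giving 4, 8, 12, 16, 20, 24, 28, 32 and 36. A session falling exactly on a survey age is counted as before the survey unless stated otherwise.

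| Assumed grid | By 12M | By 24M |
|---|---|---|
| 9 sessions, 4–36 months | 3/9 = 33% | 6/9 = 67% |
| 9 sessions, 4–24 months | 4/9 = 44% | 9/9 |
| 7 sessions, 4–24 months | 3/7 = 43% | 7/7 |
| 10 sessions, 4–24 months | 4/10 = 40% | 10/10 |
| 7 sessions, 1–24 months | 3/7 = 43% | 7/7 |
| 10 sessions, 1–24 months | 5/10 = 50% | 10/10 |
| 7 sessions at 4, 6, 9, 12, 15, 18, 24 months | 3/7 = 43% (12-month session after the survey) or 4/7 = 57% (before it) | 7/7 |

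The share before the 12M survey therefore runs from about one third to 57%, and 43% to 67% of sessions follow it. If the 12-month session in the first grid came after the survey, the lower end would be 2/9 = 22%. For the 24M wave the share is 67% if delivery runs to 36 months and essentially all if it ends at 24 months. Individual families will differ, because enrolment runs to 6 months of age and Visit 2 has a window of 90 days either side.

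**What is not affected**

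Section 7.3.2 collects demographic, home-environment, parent-health and child-development information at enrolment. Section 9.6.1 places baseline assessment before randomization. These predictors precede the sessions.

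**Comparison within the protocol**

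The mediation plan in section 9.1 orders its variables, with parent and relational effects at 12M and child outcomes at 24M. The fidelity regression has no such ordering.

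**The case against.** The strongest reply is that the regression paragraph leaves the choice open. The averaged score is a descriptive summary, and section 9.5 bases the delivery analysis on some 1125 to 1500 sessions rather than on families. Fidelity is also recorded at both follow-up visits. A statistical analysis plan could name the perception wave and the sessions. This is right as far as it goes, and it shows that the data for a correct analysis exist. It does not remove the problem. A session-level model with one perception score per family still contains sessions held before that score was taken, unless they are excluded. The protocol also commits to a predictive purpose for a variable with no baseline value.

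A reader might go further and infer that perceptions are sampled only once the sessions are over, that the regressions cannot answer their question, and that receipt and enactment have no data, so enactment should be deleted. The documents do not support this:

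- A substantial share of sessions follows the 12M survey on every grid above.
- Delivery has a stated measure, and two of the three predictor groups are available at baseline.
- Attendance is tracked (section 9.4.2) and could serve as receipt, although the protocol calls it engagement.
- StimQ and the videotaped interactions are scheduled at 12M and 24M (section 7.1.1) and could inform enactment, although both are effectiveness outcomes.

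For receipt and enactment, what is missing is a stated link to a data source. That is a detail to clarify and no reason to drop an outcome.

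**Conclusion.** The point holds for one predictor group, parents' perception. As planned, its association with fidelity cannot be read as perception predicting fidelity, because roughly one third to 57% of sessions precede the 12M measurement and most or all precede the 24M measurement. These shares rest on assumed session ages and on a survey taken at the nominal age. The conclusion that some sessions come first rests only on the stated 4-month start and the absence of a baseline measurement. The size at 24M also depends on two conflicting statements about when delivery ends, and those passages must be reconciled. Whole-period fidelity regressed on baseline family and child characteristics alone stands. The change is worth making, but it concerns an implementation analysis and not the effectiveness result.

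**What to change.** In section 9.1, Moderation of Implementation Outcomes:

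1. Regress fidelity of sessions held after the 12M assessment on the 12M perception score, adjusting for fidelity up to 12M. Splitting sessions at each family's own survey date deals with the visit window.
2. For fidelity over the whole period, use only baseline family and child characteristics as predictors. Keeping perception out of this model avoids adjusting for something that delivery may itself have changed.
3. Do not use 24M perception as a predictor of earlier sessions. Report it as an association only.
4. As a minor clarification, name the data source for receipt, for example the proportion of due sessions attended. Name a scheduled measure for enactment, stating that StimQ and observed interaction are also effectiveness outcomes.

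Separately, reconcile sections 6.1.1 and 7.1.1 on when delivery ends.

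The cost is wording. Components per session and the 12M surveys are already planned, so no new data are needed. The downside is fewer sessions per family in the perception model. Families without a 12M survey or without later sessions would contribute nothing to it directly.
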